#### Mandatory Unscheduled DSMB Review:

Study suspension is defined as a hold on recruitment. The following criteria require a review and a recommendation from the DSMB for continuation, suspension or termination of the study:

- Unexpected significant worsening of functional motor state as documented by a change at 6 months in: the MDS-UPDRS total score of > 10 points or > 5 points for the motor MDS-UPDRS subscale or an increase in H&Y of 1 or more.
- An SAE related or possibly-related to the infusion, occurring at any time post-dosing
- 2 possibly-related or related, unexpected, Grade 3 or higher Infusion-Related Allergic Reactions observed per 3 treated subjects at any time post-infusion.

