## 9. Potential Risks:

Lumbar puncture: There is some discomfort during the lumbar puncture procedure. After a brief sting from the numbing medication, the subject will feel mostly pressure or occasionally tingling sensations. The most common side effects of a lumbar puncture are headache, nausea, vomiting, or fever. In our experience, approximately 1 % of patients undergoing a lumbar puncture can develop a refractory headache (positional). Most post LP headaches respond to lying flat and resting for 48 hours and drinking plenty of fluids and caffeinated beverages as tolerated. By definition, they are refractory if they fail to resolve after these measures are taken and an autologous blood patch performed by anesthesia or neuroradiology is the treatment of choice for immediate resolution.

Blood draw: Blood draws, and infusions may cause discomfort, pain, and bruises at the site where blood is taken and sometimes causes people to feel lightheaded or to faint.

MRI scanning: All participants will be screened for metallic implants incompatible with the MRI environment. If a patient experiences unbearable claustrophobia inside MRI scanners, he/she will be removed from the scanner.

Cognitive, neurologic, and physical exams and history: These are administered by medical professionals. However, there may be some subjects embarrassed or anxious due to the questions that must be answered.

Acute immune reactions: The PI will ensure that appropriate best clinical practices and treatment are initiated should an event indicating an allergic or hypersensitive reaction occur. If this occurs, the infusion will be stopped immediately, and the subject closely monitored until stable. The suggested treatment will depend upon the grading of the reaction (NCI-CTCAE criteria). The PI will have the support of the emergency response teams from the hospital as needed. After the infusion, patients will be continuously monitored for 4 more hours, and a full neurological physical examination will be performed before discharging the patients. In case of a severe adverse event,

we can get an assessment in regards to the continuation of the study from our DSMB within 24-48 hours.

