#### **Grade 3:**

Prolonged or severe reaction (e.g., not rapidly responsive to treatment or a recurrence of reaction after an initial improvement of a Grade 1 or Grade 2 reaction).

1. Discontinue infusion immediately. Study treatment is to be discontinued
2. Administer clinical treatment for the allergic reaction as medically indicated.
3. Report as an SAE

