## 11.2 Sensitization to Donor Specific Antibodies (DSA).

There is a possibility of anti-donor alloimmune response after the first or second infusion of MSC, which might lead to a subsequent antibody-mediated rejection (AMR) with the following infusion. IF DSA are identified at either week 8 or 21 patients would be put on hold of their regular schedule on infusions and the PI will follow the algorithm describes in 11.2.1.

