## 13. Study Modification/Discontinuation

The study may be modified or discontinued at any time by the IRB, the DSMB or the FDA as part of their duties to ensure that research subjects are protected

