### **16. Data safety monitoring board (DSMB)**

An independent DSMB will monitor the conduct of the trial and subject safety based on the review of the aggregate data one-month post each infusion. The DSMB will review the aggregate data after each infusion of the initial 22 patients and determine the safety to proceed to the next infusion. The DSMB will review the aggregate data for all the patients in order to determine safety regarding neurological and physical status. At any review, the DSMB may recommend the study continues as per protocol or recommend changes to the protocol or the conduct of the study. The DSMB can recommend suspension or study termination at any time for any reason.

The DSMB Plan will be formulated and agreed upon by the Primary Investigator and DSMB Board. The DSMB will be notified within 24 hours of an SAE. All or the majority of the DSMB members will meet to discuss the SAE report promptly.

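### Section 16 defines suspension as a hold on recruitment only, so after an infusion-related trigger it does not by its terms pause the week 18 and week 36 infusions; the gap falls mainly on the 23 patients outside the DSMB's next-infusion review

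*Protocol*

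**What the plan says.** Protocol Section 16, under Mandatory Unscheduled DSMB Review, gives the definition: "Study suspension is defined as a hold on recruitment". It then lists three triggers that "require a review and a recommendation from the DSMB for continuation, suspension or termination of the study". They are unexpected motor worsening at 6 months, an SAE related or possibly related to the infusion, and two Grade 3 or higher infusion reactions per three treated subjects.

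Section 10 schedules infusions for every patient at week 0, week 18 (+/-1) and week 36 (+/-1).

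Other parts of the protocol bear on dosing:

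- **Section 16, scheduled review.** After each infusion of the first 22 patients, the DSMB looks at aggregate data and decides whether it is safe to go on to the next infusion. At any review it may also "recommend changes to the protocol or the conduct of the study", and "The DSMB can recommend suspension or study termination at any time for any reason".
- **Section 13.** "The study may be modified or discontinued at any time by the IRB, the DSMB or the FDA".
- **Section 9.** After a severe event, "we can get an assessment in regards to the continuation of the study from our DSMB within 24-48 hours".
- **Section 11.1, Grade 3.** "Discontinue infusion immediately. Study treatment is to be discontinued". Grade 4 and recurrent Grade 2 reactions also end treatment for the patient concerned.
- **Section 11.2.** If donor-specific antibodies appear, "patients would be put on hold of their regular schedule on infusions".

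**The concern.** Two of the three mandatory triggers point to harm from an infusion. The exposure that matters next is then the following infusion, both in patients already under treatment and in new recruits. Repeat dosing is also what is new here: the Phase I study in Section 3.5 gave one infusion to each of 20 patients, and Section 11.2 itself raises the possibility of a rejection reaction at the infusion that follows sensitization.

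The middle outcome, as defined, acts only on recruitment. A DSMB member could reasonably assume that suspending a repeat-infusion trial pauses its infusions, while a site following the definition would stop recruiting and keep to the infusion calendar. After the last patient has been recruited, the defined outcome has no content, although infusions are still due. At stake is whether patients who did not react receive a further infusion while a safety signal is being assessed.

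**Working it through.** The plan gives no figure on this point, so there is none to reproduce. The check is a reading of the text followed by a count.

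**Reading.** Section 11.2 shows that the protocol uses explicit dosing-hold wording where it intends a hold on infusions. Section 16 uses recruitment wording for suspension, and nothing else in the protocol text shown widens the term. The stops in Sections 11.1, 11.2 and 13.1 act on the affected patient. The next-infusion determination in Section 16 acts across patients, but by its terms for the initial 22 only.

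**Inputs.** At most 45 treated patients (Section 6.5); initial 22 (Section 16); infusions at weeks 0, 18 and 36, with 88 weeks per patient and screening from week -12 (Section 10); study period 4 years (synopsis). The recruitment rate is not stated.

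**Ceiling.** Patients outside the next-infusion determination: 45 - 22 = 23. Second and third infusions in them: 23 x 2 = 46.

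**Time available for first infusions.** 4 x 52 - 88 - 12 = 108 weeks, taking the full screening window.

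**Count just after the 45th first infusion.** Assume that first infusions are evenly spread over R weeks, so the gap is g = R/44. A patient j places before the last was first infused j x g weeks ago. Two infusions remain if j x g < 18, one if 18 <= j x g < 36, and none after that. The 23 patients are j = 0 to 22.

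| R (weeks) | g (weeks) | Patients with two due | Patients with one due | Infusions outstanding in the 23 |
|---|---|---|---|---|
| 52 | 1.18 | 16 | 7 | 2 x 16 + 7 = 39 |
| 78 | 1.77 | 11 | 10 | 2 x 11 + 10 = 32 |
| 104 | 2.36 | 8 | 8 | 2 x 8 + 8 = 24 |
| 108 | 2.45 | 8 | 7 | 2 x 8 + 7 = 23 |

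At R = 52, eight of the initial 22 (j = 23 to 30) also have one infusion due. These are left out because their next infusion is subject to the DSMB's determination. On this model the ceiling of 46 needs 22 x R/44 < 18, that is R < 36 weeks.

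**After recruitment closes.** The last patient's third infusion falls up to 36 + 1 = 37 weeks after the first. Throughout that time a suspension as defined holds nothing.

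The counts are of study infusions, not of active cells: one third of patients are allocated to placebo, and the two-dose arm has one placebo infusion. They cover patients who have had a first infusion. A patient accepted but not yet infused has three due, and the text does not say whether a recruitment hold stops the first of these.

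**The case against.** The strongest reply is that dosing is already under DSMB control. For the initial 22 patients the next infusion needs a DSMB safety determination, whatever suspension means. Section 16 also provides for aggregate review a month after each infusion and for review of data from all patients. The three named outcomes need not be exclusive: a mandatory unscheduled review is still a review, so the DSMB may recommend a dosing pause as a change in conduct, alone or with a recruitment hold. The board hears of an SAE within 24 hours and meets promptly. Section 13 adds the IRB and FDA. The DSMB Plan is not shown and may deal with infusions in progress.

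Most of this stands, and it sets the size of the point. A reader might infer that the DSMB cannot stop dosing, or that all 45 x 2 = 90 later infusions would run on unchecked. The documents do not support either inference: the board has several routes to dosing, and 22 of the 45 patients have an explicit next-infusion determination. Nor would a patient with a Grade 3 or 4 reaction go on being dosed, since Section 11.1 ends that patient's treatment.

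What the reply does not reach is the definition. The next-infusion determination does not by its terms cover the other 23 patients. The change-in-conduct route works only if someone notices that suspension leaves infusions untouched. A DSMB Plan that gave the term a wider meaning would depart from the protocol and leave the protocol in need of alignment.

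**Conclusion.** The point holds as a defect in the scope of a defined term. A recommendation of suspension after an infusion-related SAE or clustered Grade 3 or higher reactions does not, as written, pause later infusions in patients under treatment, and after recruitment closes it has no effect.

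The exposed group is mainly the 23 patients outside the next-infusion determination, with at most 46 second and third infusions. Just after the last first infusion, about 23 to 39 would be outstanding. That range assumes even spacing of first infusions over 52 to 108 weeks; it also assumes that the DSMB says nothing separate about dosing and that the limit to the initial 22 patients is read literally.

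Severity is minor, on grounds of patient safety. It is worth correcting because the text is explicit, the error runs in the unsafe direction and the correction is cheap.

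**What to change.** In Section 16, under Mandatory Unscheduled DSMB Review, define suspension as a hold on recruitment and, unless the DSMB states otherwise, on all outstanding study infusions in enrolled patients until the DSMB recommends resuming. State that safety and follow-up visits continue. The exception keeps a recruitment-only hold available, for example after the motor-worsening trigger. Align the DSMB Plan with this wording and say how infusions delayed past the +/-1 week window are handled.

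The cost is one sentence in the protocol and matching text in the DSMB Plan. The downside is that some infusions may fall outside their window if a suspension occurs.

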## 17. Intellectual Property and data sharing:

As a naturally occurring unmodified cell that exists in the bone marrow, our proposed mesenchymal stem cells cannot be patented (Leahy-Smith America Invents Act (AIA), Pub. L. 112-29, sec. 33(a), 125 Stat. 284). The MSC manufactured rights belong to the Center for Cell and Gene Therapy at Baylor College of Medicine. All the biospecimens, neuro-imaging, and measurements collected for this study are considered the intellectual property of the University of Texas Health Science Center at Houston.

The results of this study will be published in a scientific journal and will be presented at national and international scientific meetings. A summary of the results will be available in clinical trial.gov, Research Match, and Fox Trial Finder website. Additionally, we will send a newsletter to our patients at the end of the study.

## 18. Ethics

This protocol will be submitted and review by the local Institutional Review Board:

The Committee for the Protection of Human Subjects  
 The University of Texas Health Science Center at Houston  
 [name]  
 [name]  
 Institutional Official: [name] FWA# 00000667  
 IRB Registration Numbers: IRB00000308, IRB00003763, IRB00004604, IRB00008445

In addition, the study will be conducted according to the standards that meet Good Clinical Practice (GCP). These standards respect the following guidelines:

1. Guideline for Good Clinical Practice (International Conference on Harmonization ICH of Technical Requirements for the Registration of Pharmaceuticals for Human Use).
2. United States (US) Code of Federal Regulations (CFR) dealing with clinical studies (21 CFR

Parts 50, 54, 56, 312, 314, and 511).

3. Declaration of Helsinki, concerning medical research in humans (“Recommendations Guiding Physicians in Biomedical Research Involving Human Subjects,”) Helsinki 1964, amended Tokyo 1975, Venice 1983, Hong Kong 1989 and revised version of Somerset West, Republic of South Africa, October, 1996, Note of Clarification added by the WMA World Medical Association General Assembly, Washington 2002, Note of Clarification added by the WMA General Assembly, Tokyo 2004

## 19. Consent

The consent form will describe the purpose of the study, the procedures to be followed, and the risks and benefits of participation. Potential subjects are to be fully explained the protocol and study procedures and allowed them to ask any questions. All subjects must sign the IRB approved informed consent form before performing any study-related activity (including screening activities). For subjects who cannot consent for themselves the legally authorized representative (LAR) must sign the consent form. The original signed consent form is to be placed in the subject’s study file. A copy of the signed consent form is to be given to subjects or LAR for their records.

Prior to obtaining written informed consent, subjects will be asked to be in the OFF- medication state (i.e. hold PD medications) for at least 8-12 hours before coming to the screening visit appointment. Subjects will be asked to bring their PD medications to the CRU. After performing an OFF-state neurological exam (Modified H&Y and MDS-UPDRS), subjects will be asked to take their PD medications with a snack, wait for an hour, and then the motor section of the MDS-UPDRS) will be repeated in the ON-medicine state to assess improvements in motor symptoms. Subjects will be emailed written instructions on how to prepare for the screening visit and their response will be considered as their willingness and verbal consent to preparation.

## **Appendix A. UK PARKINSON’S DISEASE BRAIN BANK CRITERIA**

### Step 1. Diagnosis of Parkinsonian Syndrome

- Bradykinesia
- At least one of the following
  - Muscular rigidity
  - 4-6 Hz rest tremor
  - postural instability not caused by primary visual, vestibular, cerebellar, or proprioceptive dysfunction

### Step 2 Exclusion criteria for Parkinson's disease

- history of repeated strokes with stepwise progression of parkinsonian features
- history of repeated head injury
- history of definite encephalitis
- oculogyric crises
- neuroleptic treatment at onset of symptoms
- more than one affected relative
- sustained remission
- strictly unilateral features after 3 years
- supranuclear gaze palsy
- cerebellar signs
- early severe autonomic involvement
- early severe dementia with disturbances of memory, language, and praxis
- Babinski sign
- presence of cerebral tumor or communication hydrocephalus on imaging study
- negative response to large doses of levodopa in absence of malabsorption
- MPTP exposure

### Step 3 supportive prospective positive criteria for Parkinson's disease

Three or more required for diagnosis of definite Parkinson's disease in combination with step one

- Unilateral onset
- Rest tremor present
- Progressive disorder
- Persistent asymmetry affecting side of onset most
- Excellent response (70-100%) to levodopa
- Severe levodopa-induced chorea
- Levodopa response for 5 years or more
- Clinical course of ten years or more

*\*From: Hughes AJ, Daniel SE, Kilford L, Lees AJ. Accuracy of clinical diagnosis of idiopathic Parkinson's disease. A clinico-pathological study of 100 cases. JNNP 1992;55:181-184.*

## Appendix B. Modified Hoehn and Yahr

---

## Modified Hoehn and Yahr Scale

---

- 1.0: Unilateral involvement only
  - 1.5: Unilateral and axial involvement
  - 2.0: Bilateral involvement without impairment of balance
  - 2.5: Mild bilateral disease with recovery on pull test
  - 3.0: Mild to moderate bilateral disease; some postural instability; physically independent
  - 4.0: Severe disability; still able to walk or stand unassisted
  - 5.0: Wheelchair bound or bedridden unless aided
-

## Appendix D. MSC label sample

### LABELS

#### Partial Label for Final Product

To be used during preparation for administration

|                                                |
|------------------------------------------------|
| MSC, CULTURED, THAWED & WASHED                 |
| LOT#: C2334.5 Expiration: 16.00h 03/14/16      |
| RECIPIENT: DOE, John HeMH 0987654 P12345       |
| For use by intended recipient only             |
| CAUTION: New drug for investigational use only |

#### Full Label

To be used for final product

| TCH-MSC CULTURED - Thawed and Washed,                                                                                                                                                                                             |                                                                         |                                                                                                                                                          |            |
|-----------------------------------------------------------------------------------------------------------------------------------------------------------------------------------------------------------------------------------|-------------------------------------------------------------------------|----------------------------------------------------------------------------------------------------------------------------------------------------------|------------|
| Component #:

C2334.5
[figure not shown]                                                                                                  | Collection Date and Time
13.00h 11/06/12                      | Nonreactive for HBsAg by FDA required test. Non-reactive for syphilis by STS. Negative by a test for antibody to HIV. No unexpected antibodies detected. | n/a |
|                                                                                                                                                                                                                                   | Expiration Date and Time
17.00h 11/06/12                      |                                                                                                                                                          |            |
| Total Vol. (ml): _____

Total Cells _____

Recipient Wt:(kg) 75                                                                                                                           | DO NOT IRRADIATE

DO NOT USE LEUKO-REDUCTION FILTER | Product Contains Plasma Lyte

Vol / Units 50ml                                                                                       |            |

## Appendix E. Medication Form

| MEDICATION FORM |                                                    |                                              |                                                                          |                                                                     |                           |                           |                          |                             |                                                |
|-----------------|----------------------------------------------------|----------------------------------------------|--------------------------------------------------------------------------|---------------------------------------------------------------------|---------------------------|---------------------------|--------------------------|-----------------------------|------------------------------------------------|
| Patient's name: |                                                    |                                              |                                                                          | Scr Date
(mm/dd/yy)                                              | Inf #1 Date
(mm/dd/yy) | Inf #2 Date
(mm/dd/yy) | Inf#3 Date
(mm/dd/yy) | DOB(mm/dd/yy):              |                                                |
| Subject ID:     |                                                    |                                              | Allergies:                                                               |                                                                     |                           |                           |                          |                             |                                                |
| Visit #         | Medication Name
(List generic name if possible) | Dosage Units
(mg, drops, mcg, puffs, etc) | Frequency
(QD, BID, TID, QID, QOD, one time, pm, once per week/month) | Route
(PO, topical, IM, IV, SC, rectal, intranasal, intraocular) | Indication                | X if for PD               | Start Date               | Stop Date
(X if ongoing) | Reason, if changed
(increase, decrease, DC) |
|                 |                                                    |                                              |                                                                          |                                                                     |                           |                           |                          |                             |                                                |
|                 |                                                    |                                              |                                                                          |                                                                     |                           |                           |                          |                             |                                                |
|                 |                                                    |                                              |                                                                          |                                                                     |                           |                           |                          |                             |                                                |
|                 |                                                    |                                              |                                                                          |                                                                     |                           |                           |                          |                             |                                                |
|                 |                                                    |                                              |                                                                          |                                                                     |                           |                           |                          |                             |                                                |
|                 |                                                    |                                              |                                                                          |                                                                     |                           |                           |                          |                             |                                                |
|                 |                                                    |                                              |                                                                          |                                                                     |                           |                           |                          |                             |                                                |
|                 |                                                    |                                              |                                                                          |                                                                     |                           |                           |                          |                             |                                                |
|                 |                                                    |                                              |                                                                          |                                                                     |                           |                           |                          |                             |                                                |
|                 |                                                    |                                              |                                                                          |                                                                     |                           |                           |                          |                             |                                                |

\*Visit #: 1 = Scr, 2 =BL, 3 = inf # 1, 4 = wk 7, 5 = inf# 2, 6 = wk 20, 7 = inf# 3, 8 = wk 29, 9 = wk 39, 10 = wk 52, 11 = wk 78, or phone visit = Pv date

